## Methods/design

### Study design

This is a 2 × 2 factorial design that accomplished as a randomized double-blind, placebo-controlled clinical trial. The Standard Protocol Items: Recommendations for Interventional Trials (SPIRIT) 2013 Statement will be followed in this trial (Additional file 1) [36].

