### Participants (inclusion and exclusion criteria)

Patients will be recruited in the study after fulfilling certain criteria, including: overweight and obese (BMI 25–40 kg/m^2^) individuals aged 18–60 years of both genders, existence of NAFLD by ultrasound, NAFLD activity score < 3, and willingness to participate by signing an informed consent document, Patients with viral hepatitis, cirrhosis, Wilson’s disease, pregnancy acute fatty liver, hepatocellular carcinoma, hypothyroidism and a history of chronic liver disease, lipodystrophy, menopause, parenteral nutrition, bladder and bile duct disease, significant weight loss (≥ 10% of body weight in preceding six months) or weight loss due to surgery, congenital metabolic diseases, individuals on antioxidant supplementations, milk thistle, and omega-3 fatty acids in the previous six months, a history of liver-damaging drugs (amiodarone, anti-virus, aspirin, non-steroidal anti-inflammatories, corticosteroids, methotrexate, tamoxifen, tetracycline, valproic acid), alcohol consumption > 20 g/day, calorie intake < 800 kcal or > 4200 kcal a day, pregnancy and lactation, serum ALT levels more than five times the upper limit (maximum limit of 30 for women and 40 for men), or history of cardiovascular and kidney disease (urine analysis albumin ≥ 30 mg/24 h and GFR ≤ 90 mL/min/1.73 m^2^) will be not included.

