### Primary outcome measures

Fasting venous blood samples will be taken from patients on the morning of admission and on day 85. Primary outcomes including serum high-sensitive C-reactive protein (CRP) (μg/mL) and adiponectin (μg/mL) will be measured by high-sensitivity enzyme-linked immunosorbent assay (ELISA) with the following characteristics: hs-CRP (BioVendor, Heidelberg, Germany; #RH961CRP01HR); adiponectin (ALPCO Immunoassays, Salem, NH; #47-ADPHU-E01). Plasma insulin (IU/mL) (Pars Azmoon Co., Tehran, Iran), β-CX (HPLC- Column18), and free fatty acids (NEFA C Assay Kit; Wako Chemicals, Neuss, Germany, respectively) as other primary outcomes will be measured by the colorimetric methods. The enzymatic method (Pars Azmoon2 Co., Tehran, Iran) will be used for measuring serum hepatic enzymes (including ALT, AST, and ALP). IR will be assessed by homoeostasis model-insulin resistance index (HOMA-IR) [41], according to the following formulas: HOMA-IR [42] will be calculated using the formula “fasting insulin value fasting blood sugar level/405,” equivalent to the HOMA-formula: HOMA = fasting serum insulin (μU/mL) × fasting plasma glucose (mM/L)/22.5 [42]. HbA1c will be measured by spectrophotometry using the Biorad1 IN2IT devices. Glycemic status (fasting blood glucose) will be determined by the glucose oxidase/peroxidase (GOD-Perid) method using commercially available kits (Pars Azmoon Co., Tehran, Iran).

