### Statistical analysis

Two populations will be used in the analyses. The intention-to-treat (ITT) population includes all patients who will be randomized, while the per-protocol (PP) population includes all individuals who complete the 12-week intervention (i.e. study completers). The data will be checked for plausibility by randomly checking the accuracy and completeness and verifying against source data. The variables will be tested for normality using the Kolmogorov–Smirnov test, the Shapiro–Wilk test, and normality plots. All quantitative data will be reported as mean ± standard deviation. Baseline characteristics of participants will be compared among groups using analysis of variance (ANOVA) for parametric data and the Kruskal–Wallis test for non-parametric data. The primary analysis, comparing the effects of treatment on primary outcomes of fatty liver over 12 weeks, will be conducted using a generalized linear mixed-models procedure. Treatments and time will be included as fixed effects and the interactions between interventions and time will be tested. If significant main effects or interaction effects are observed, post-hoc analysis with Bonferroni adjustments will be performed. Potential confounding factors and effect modifiers (e.g. baseline age and gender, etc.) will be investigated within the model. Logistic regression will be used to test the multiplicative interaction. Rothman’s synergy index, which would be equal to unity under additively, and less than unity when suggesting antagonism, will be utilized to examine the postulated interaction effect of a HPD and β-CX on fatty liver. The secondary analysis, comparing the effects of treatment on secondary outcomes of fatty liver over 12 weeks, will be conducted using the same procedure. Potential confounding factors and effect modifiers will be investigated within the model. Differences between participants who complete and withdraw from the trial will be analyzed using an independent t test or the Mann–Whitney test for continuous variables (e.g. age) and chi-square for categorical variables (e.g. gender). Associations between severity of fatty liver and nutritional status at baseline will be assessed using regression analysis. McNemar’s test will be used to analyze the binary variables before and after the intervention. Our statistical analyses will be performed by using SPSS 21 (IBM, Armonk, NY, USA) and the results will be considered significant at *P* < 0.05.

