### Sample size and sampling

The sample size was calculated based on the primary outcome measures (12-week change in serum adiponectin, CRP, FFA, insulin, serum β-CX, FBS). Using the standard deviations reported in previous studies [17, 20, 47, 48], a maximum sample size of 18 individuals per group will be selected with mean changes of adiponectin as much as 1.3 and standard division of 1.4 g/day and 30% attrition rate. It calculated by pass 11.

To achieve the target sample size, all patients who will come to the gastrology clinic of Ahvaz hospitals will be included in the study if they will be willing to participate in the study considering the inclusion criteria of the study.

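### The two analyses named for the HPD × β-CX interaction need a binary fatty-liver event that the outcome sections do not define, and the mixed model states no HPD × β-CX term

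*Protocol article*

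**What the plan says.** All points are from the protocol article.

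- **Study design:** "This is a 2 × 2 factorial design that accomplished as a randomized double-blind, placebo-controlled clinical trial".
- **Statistical analysis, interaction:** "Logistic regression will be used to test the multiplicative interaction"; this sentence names no outcome. Rothman's synergy index "will be utilized to examine the postulated interaction effect of a HPD and β-CX on fatty liver".
- **Statistical analysis, primary model:** a generalized linear mixed model with treatments and time as fixed effects and tests of intervention-by-time interactions. No diet-by-supplement term is named.
- **Primary outcome measures:** "Primary outcomes including serum high-sensitive C-reactive protein (CRP) (μg/mL) and adiponectin (μg/mL) will be measured". The section goes on to insulin, serum β-CX, free fatty acids, ALT, AST, ALP, HOMA-IR, HbA1c and fasting glucose.
- **Secondary outcome measures:** anthropometry, blood pressure, body composition, lipids and malondialdehyde.
- **Sample size and sampling:** based on "12-week change in serum adiponectin, CRP, FFA, insulin, serum β-CX, FBS".
- **Participants:** entry requires "existence of NAFLD by ultrasound, NAFLD activity score < 3". This is the only mention of ultrasound in the text.

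**The concern.** Logistic regression models the probability of an event, and the synergy index is computed from relative risks or odds ratios of an event. The outcome sections supply no event. Every listed outcome is continuous, and none records whether, or to what degree, the liver is fatty. All participants have fatty liver at entry, so an event would have to be something like resolution or a drop in grade at 12 weeks, and the article defines neither.

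The interaction is described as postulated, so it is a stated hypothesis. If the section is followed literally, the analyst must construct a binary variable once data are in hand, with free choice of marker, cut-off, time point and scale. That opens the interaction result to selection, and dichotomising a continuous marker discards information in a small trial.

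**Working it through.** **1. Methods against outcomes**

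| Analysis | Needs | Supplied by the article |
|---|---|---|
| Logistic regression, multiplicative interaction | Binary event | No outcome named |
| Synergy index, additive interaction | Binary event, and risk or odds scale | Fatty liver named; no event, cut-off, time point or scale |
| Mixed model | Outcome and model terms | Continuous outcomes; treatment, time and intervention × time; no HPD × β-CX term |

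The only analyses assigned to the HPD × β-CX interaction are the two without a defined outcome.

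**2. The plan's own sample size.** Inputs from Sample size and sampling: difference 1.3, SD 1.4 (taken in the same unit), 18 per group, 30% attrition. Two-sided 0.05 and 80% power are assumed, because neither sidedness nor power is stated.

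n = 2 × (1.4/1.3)² × (1.96 + 0.84)² ≈ 18.2, or 19 per group when rounded up. Power at 18 per group is 79.6% (normal) or 77.2% (t). The stated 18 is therefore reproduced to within one or two patients, as a two-group comparison of a continuous marker. No event rate and no interaction enters it.

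**3. The interaction on the continuous outcome.** The contrast is (HPD+β-CX − HPD+placebo) − (NPD+β-CX − NPD+placebo), where NPD is the normal protein diet. With n evaluable per arm, SE = 1.4 × √(4/n). Three values of n are shown: 23 (92/4, from the abstract), 18 (sample size section) and 16 (23 × 0.70 = 16.1).

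| n per arm | SE | 95% CI half-width (1.96 × SE) | Power for 1.3 (t, 4n − 4 df) | Detectable at 80% (2.80 × SE) |
|---|---|---|---|---|
| 16 | 0.70 | 1.37 | 45% | 1.96 |
| 18 | 0.66 | 1.29 | 49% | 1.85 |
| 23 | 0.58 | 1.14 | 60% | 1.64 |

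For 80% power at 1.3: n = 4 × (1.4 × 2.80/1.3)² ≈ 36.4, or 37 evaluable per arm.

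**4. The interaction on a binary outcome.** The article gives no event rate, so its power cannot be computed. As a favourable assumption, take 50% events in every arm. The SE of the log ratio of odds ratios is √(4/(n × 0.25)): 1.00, 0.94 and 0.83 for n = 16, 18 and 23. The ratio of odds ratios detectable with 80% power is exp(2.80 × SE), about 16, 14 and 10.

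**5. Why the scale must be fixed.** Illustration with assumed 12-week fatty-liver rates of 0.90 (control), 0.70, 0.70 and 0.40 (both), control as reference:

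- Risk ratios 0.778, 0.778, 0.444: S = (0.444 − 1)/[2 × (0.778 − 1)] = 1.25.
- Odds ratios 0.259, 0.259, 0.074: S = (0.074 − 1)/[2 × (0.259 − 1)] = 0.63.

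The same rates fall on opposite sides of 1. The event is common in a population that all has it at entry, so odds ratios do not approximate risk ratios.

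**The case against.** The strongest reply is that this is a condensed article. The event may be defined in the full protocol or analysis plan. The assessment schedule (Fig. 2) could not be seen in the text reviewed and may list a follow-up ultrasound. The section also refers to fatty-liver severity at baseline and to unnamed binary variables. ALT and AST are listed outcomes, and the Background links them to severity. This limits the claim: a later scan cannot be excluded. It does not remove the mismatch, because the article itself commits the interaction to binary methods while its outcome lists contain no binary endpoint, and liver enzymes are indirect, continuous markers.

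Several stronger readings are tempting but not supported:

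- **The trial cannot answer its central question.** The article does not say that interaction is why a factorial design was chosen; such a design also serves two main effects. If treatments enter the mixed model as a four-level factor, the contrast in the working can be derived from the planned fit. It is unstated, not unobtainable.
- **The synergy index can be turned into synergy or antagonism by choosing the reference arm.** With relative risks of 1.0, 0.6, 0.6 and 0.3, S is 0.7/0.8 = 0.875 against control and about 1.17 against the combined arm. But the article names NPD + placebo as the control group, and against it 0.875 correctly describes a joint reduction smaller than the sum of the two.
- **McNemar's test is offered in place of a comparison between arms.** The article says only that the "test will be used to analyze the binary variables before and after the intervention". Nothing says that it replaces the between-arm analysis.

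**Conclusion.** The point holds for the two named interaction analyses: they have no defined outcome in the article, and the model that does have outcomes states no HPD × β-CX term. The primary analysis, the sample size and the main treatment comparisons do not depend on these sentences, so this is a should-fix matter.

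The conclusion about the mismatch rests on the text alone. The power figures of about 45%, 49% and 60% assume two-sided 0.05, SD 1.4 in every arm and an interaction as large as the 1.3 used for sizing. A smaller interaction would have lower power. The binary-outcome figures are illustrations under assumed rates.

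**What to change.** Replace the logistic regression and synergy-index sentences with one that states an HPD × β-CX term in the planned mixed model for the continuous primary outcomes, or HPD × β-CX × time where baseline is kept as a response. Report it as the difference of differences with a 95% CI, which measures departure from additivity directly. Say that the trial was not sized for this contrast and that the result is to be read as an estimate.

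Keep a logistic or synergy analysis only as supportive, and only if the binary event, cut-off, time point, scale and the NPD + placebo reference are all fixed before the randomization codes are opened.

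The cost is a few rewritten sentences, with the same data and software. The downside is a visibly wide interval: a half-width of roughly 1.1 to 1.4 on adiponectin, against a sizing difference of 1.3.

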### Sample size and sampling

The sample size was calculated based on the primary outcome measures (12-week change in serum adiponectin, CRP, FFA, insulin, serum β-CX, FBS). Using the standard deviations reported in previous studies [17, 20, 47, 48], a maximum sample size of 18 individuals per group will be selected with mean changes of adiponectin as much as 1.3 and standard division of 1.4 g/day and 30% attrition rate. It calculated by pass 11.

To achieve the target sample size, all patients who will come to the gastrology clinic of Ahvaz hospitals will be included in the study if they will be willing to participate in the study considering the inclusion criteria of the study.

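### The protocol names six primary outcomes in one section and places eleven under the primary heading in another, states no error control across them, and includes the supplement's own serum level

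*Protocol article*

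**What the plan says.** All references are to the protocol article.

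- **Section on sample size.** Six primary outcomes are named here: "The sample size was calculated based on the primary outcome measures (12-week change in serum adiponectin, CRP, FFA, insulin, serum β-CX, FBS". The 18 per group are then derived from adiponectin, as the largest requirement among them.
- **Primary outcome measures.** The section opens with "Primary outcomes including serum high-sensitive C-reactive protein (CRP) (μg/mL) and adiponectin (μg/mL) will be measured". Plasma insulin, β-CX and free fatty acids follow "as other primary outcomes will be measured by the colorimetric methods". These five are called primary in words. Under the same heading come "serum hepatic enzymes (including ALT, AST, and ALP"), then "IR will be assessed by homoeostasis model-insulin resistance index (HOMA-IR"), then "HbA1c will be measured by spectrophotometry", and finally fasting blood glucose. That makes eleven variables.
- **Supplement level as an outcome.** The text "β-CX (HPLC- Column18), and free fatty acids" puts the supplement's own blood level among the outcomes labelled primary, and the sample size section repeats it.
- **Statistical analysis.** One mixed-model procedure is applied to the primary outcomes, and "the results will be considered significant at" P < 0.05. Bonferroni is tied to post-hoc analysis once a main or interaction effect is significant. The section gives no hierarchy, co-primary rule or split of alpha.

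**The concern.** Three features combine.

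1. The article does not settle what is primary. Five, six and eleven are all defensible counts, which leaves room to decide after the data are seen which results carry the primary label.
2. Each primary outcome is judged at the full 5%. The Bonferroni step acts only after an outcome has already passed an unadjusted test, so it does not limit the chance that some primary outcome passes by luck.
3. Serum β-CX is measured in a trial where two of the four groups take β-CX daily. A rise shows that capsules were taken and absorbed. It says nothing about fatty liver, yet as written it could be reported as a positive primary result for the β-CX factor.

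In addition, HOMA-IR is calculated from fasting insulin and fasting glucose, both also listed, so one signal can appear up to three times.

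**Working it through.** **1. Count of primary outcomes**

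| Source | Variables | Count |
|---|---|---|
| Called primary in words (primary outcome section) | hs-CRP, adiponectin, insulin, β-CX, FFA | 5 |
| Sample size section | those five plus FBS | 6 |
| All variables under the primary heading | those six plus ALT, AST, ALP, HOMA-IR, HbA1c | 11 |

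The lists are nested: all six in the sample size section also appear under the primary heading.

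**2. The plan's own sample size**

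Inputs from the sample size section are a difference of 1.3 and an SD of 1.4. Two-sided testing at 0.05 and 80% power are my assumptions, because the article states neither sidedness nor power.

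n = 2 × (1.4/1.3)² × (1.960 + 0.842)² = 18.2 per group (19 rounded up; the article states 18).

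Power at 18 per group: 1.3 / (1.4 × √(2/18)) = 2.786, and Φ(2.786 − 1.960) = 79.6%.

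So 18 is close to what a single outcome needs at an unadjusted 0.05. It leaves nothing for multiplicity.

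**3. Chance of at least one false-positive primary**

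This assumes one 5% test per outcome and all null hypotheses true. If the outcomes are independent, the chance is 1 − 0.95^k. The correlated rows assume equicorrelated normal test statistics. The documents give no correlations, so a range is shown.

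| Pairwise correlation | k = 6 | k = 11 |
|---|---|---|
| 0 | 26.5% | 43.1% |
| 0.3 | 24% | 37% |
| 0.5 | 21% | 30% |
| 0.7 | 16% | 22% |

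Dropping β-CX alone leaves 1 − 0.95^5 = 22.6% and 1 − 0.95^10 = 40.1% under independence. Reclassifying that one variable therefore does not resolve the multiplicity.

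**4. Serum β-CX**

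The article gives no expected rise and no SD, so any figure is conditional. With 36 against 36 (two groups of 18 on each side of the β-CX factor), power to detect a difference in serum β-CX at 0.05 is:

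- 56% for a rise of 0.5 SD
- 92% for 0.8 SD
- 99% for 1.0 SD

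**5. Power if several primaries are kept**

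Holm's first step uses 0.05/k. For adiponectin at 18 per group:

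- k = 6: threshold 0.00833, critical value 2.638, Φ(2.786 − 2.638) = 56%
- k = 11: threshold 0.00455, critical value 2.838, Φ(2.786 − 2.838) = 48%

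Restoring 80% at those thresholds needs 29 or 32 per group before attrition. All figures use the normal approximation.

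**The case against.** **A rule across outcomes may sit in a document not shown.** The full protocol or analysis plan could contain one, and the Bonferroni sentence does not define its family. This is fair as far as it goes. What remains is what the article itself fixes: two lists of different length, a 0.05 threshold for the primary outcomes, an adjustment triggered only after significance, and an exposure measure labelled primary.

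**Eleven is only the heading count.** The last six variables in that section read as assay and formula descriptions. This stands in part. On the six-outcome reading the inflation is 21–26%, not 30–43%. That is still at least four times the stated 5%.

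**A stronger reading does not hold.** A reader might infer that a positive primary result is almost certain. Multiplicity alone does not give that. It would need a large rise in serum β-CX, which the article does not quantify, and a rule that any single significant primary counts as success, which the article does not state. If ten other outcomes were null and independent, the chance of at least one significant result would run from about 74% (rise of 0.5 SD) to 95% (0.8 SD). In any case a β-CX rise says nothing about the high protein factor.

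**Counting several effects per outcome as independent tests would also overstate the error.** HOMA-IR is built from insulin and glucose, so independence across all eleven is impossible. The model is described as treatments, time and their interactions, not as a fixed set of separate factorial tests.

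**The choice of adiponectin belongs to the investigators.** It set the sample size because it needed the largest number, which does not make it the most important outcome. This stands.

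**Conclusion.** The point holds. As written, the article leaves the primary set at five, six or eleven variables and states no control across them. The chance of at least one false-positive primary is about 26% (six) or 43% (eleven) under independence, and about 21–24% or 30–37% at pairwise correlations of 0.5–0.3. These figures assume one two-sided 5% test per outcome and no true effects.

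Separately, serum β-CX measures exposure. If supplementation raises it appreciably, it could be reported as a primary success for the β-CX factor with no effect on NAFLD. How likely that is cannot be computed from the article. The size calculation supports one primary outcome at 0.05 and does not support six or eleven.

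**What to change.** Make a dated amendment before unblinding. The article describes the trial as ongoing, with codes closed until all participants complete.

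1. Make the primary outcome section and the sample size section list the same outcomes.
2. Reclassify serum β-CX as an exposure or adherence marker.
3. Name one primary outcome. Twelve-week change in adiponectin is the natural candidate, because the 18 per group already rest on it at an unadjusted 0.05. The investigators should confirm or justify another choice.
4. Make the remaining outcomes secondary, with Holm or false-discovery-rate control, and note that HOMA-IR is derived from insulin and glucose.

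This multiplicity correction adds no patients. Because the trial is registered and under way, changing the primary set is a substantive amendment and should be recorded as such. The downside is that fewer results can be called primary.

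If several primaries are kept with Holm across them, the amendment should state the power cost. At 18 per group, power for adiponectin at the first-step threshold is about 56% (six) or 48% (eleven), against about 80% at 0.05.

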**Methods/design:**

This study will be conducted as a randomized, double-blind, placebo-controlled clinical trial for 12 weeks to receive daily β-CX 6 mg supplementation combined with a HPD on levels of metabolic factors, β-CX, glycemic and lipid profiles, inflammatory factors, adipocytokines, and body composition. Ninety-two eligible patients, aged 18–60 years, of both genders, who are obese and overweight (body mass index [BMI] 25–40 kg/m^2^) will be randomly assigned to four groups as follow: HPD + placebo; normal protein diet + β-CX (NPD + β-CX); HPD + β-CX; and NPD + placebo (control group). Two populations will be analyzed in this work. The intention-to-treat (ITT) population includes all patients who will be randomized, while the per-protocol (PP) population includes all individuals who complete the 12- week intervention (i.e. study completers).

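### The 18 per group shows no allowance for the Bonferroni post-hoc comparisons: an adjusted pairwise adiponectin difference of 1.3 has about 53–63% power

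*Protocol article*

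**What the plan says.** Under Sample size and sampling, the protocol article sets "a maximum sample size of 18 individuals per group will be selected with mean changes of adiponectin as much as 1.3 and standard division of" (the SD being 1.4), with a "30% attrition rate". The only detail of method is "It calculated by pass 11". No test, alpha, sidedness, power or multiplicity allowance is printed there. The abstract gives 92 patients in four groups, that is 23 each, and Study design calls the trial a 2 × 2 factorial.

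Under Statistical analysis, the primary analysis is a mixed model: "Treatments and time will be included as fixed effects and the interactions between interventions and time will be tested". The next step is conditional: "If significant main effects or interaction effects are observed, post-hoc analysis with Bonferroni adjustments will be performed". The general threshold is that "the results will be considered significant at *P* < 0.05". The section does not say how many comparisons the Bonferroni step covers.

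**The concern.** With four arms, a significant overall test shows only that some arms differ. Under the printed text, a statement that a particular arm differs from control would come from the Bonferroni step. Nothing in the sizing paragraph covers that step. A true difference of the planned size between an active arm and control could therefore fail the adjusted test in roughly 37–47% of trials (100 − 63 to 100 − 53). A reader who takes the sample size as adequate could then read that result as no effect.

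**Working it through.** **Inputs.**
- From the sizing paragraph: difference δ = 1.3, SD σ = 1.4, n = 18 per group. The printed unit does not fit serum adiponectin, but only the ratio δ/σ = 0.929 matters here.
- From the abstract: 92 randomised, so 23 per group.
- From the analysis section: threshold 0.05.
- Assumed: two-sided testing; 1.3 is a between-group difference in 12-week change; 1.4 is the SD of that change. The Bonferroni step covers three comparisons (each arm against control) or six (all pairs).

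**Is 18 the number before or after attrition?** 18 × 1.3 = 23.4, close to the 23 randomised per group, so 18 is read as the evaluable number.

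**Reproducing 18.**
- Two-group normal formula at 80% power: n = 2(1.960 + 0.842)²(1.4/1.3)² = 18.2. The exact t test needs 20.
- Four-group F test at 5%, one arm 1.3 away from the other three: Σ(μᵢ − μ̄)² = 0.75 × 1.3² = 1.2675, so λ = 18 × 1.2675/1.4² = 11.64. Power is 80.3% at n = 18 and 77.6% at n = 17.

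Both fit at about 80% power. Neither includes a Bonferroni divisor.

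**Power for one pair at n = 18.** The noncentrality is 0.929 × √(18/2) = 2.786. By the normal approximation:
- at 0.05: Φ(2.786 − 1.960) = 79.5%
- at 0.05/3: Φ(2.786 − 2.394) = 65.2%
- at 0.05/6: Φ(2.786 − 2.638) = 55.9%

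The noncentral t with error pooled over four groups (4n − 4 df, so 68 at n = 18) gives slightly lower figures:

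| Evaluable per group | Unadjusted | 3 comparisons | 6 pairs |
|---|---|---|---|
| 18 | 78% | 63% | 53% |
| 23 (all randomised) | 88% | 76% | 67% |
| 92 × 0.7/4 = 16.1 | 74% | 57% | 47% |

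**The written sequence, simulated at n = 18** (overall test at 0.05, then Bonferroni over six, for the pair differing by 1.3): 52–53%, whether one arm differs, two arms differ, or the two middle arms lie halfway. With a divisor of three after the overall test, power is 57% in the halfway pattern and about 62% when one arm differs. It is 63% when two arms share the effect.

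**Size needed for 80% under Bonferroni.** The normal formula gives 24.3 evaluable per group for three comparisons and 28.1 for six.

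**Why a step-down test is valid here.** If all four arms are equal, the overall test limits false claims to 5%. If they are not all equal, at most three of the six pairwise nulls can be true (three arms equal, one different). Among the three comparisons with control, at most two can be true. Starting at 0.05/3 or 0.05/2 therefore keeps familywise error at or below 5%. In simulation of the six-pair version it was at most about 4.9%.

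**The case against.** Four points deserve weight.

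*The document does not reveal the sizing test.* A reader might infer that 18 came from a single two-group comparison. The figures do not support that: a four-group overall test needs exactly 18 for 80%, at least as good a fit, and it is close to what the plan tests first. This point stands. The gap remains, because neither test covers the adjusted comparisons.

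*Bonferroni is a conditional follow-up, not the primary rule.* This also stands. Sizing on the main model test is ordinary practice, and that test takes no Bonferroni penalty: 80% at 18 per group if one arm differs, though 61% if the middle arms lie halfway. Passing through a first test cannot, however, raise the power of the pairwise step.

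*Six pairs is an assumption.* Correct. A flat fall from 78% to 53% would overstate what the article says. The honest statement is the range 53–63%.

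*The design is factorial.* If each factor were tested on its margin, 36 against 36, a main effect of 1.3 would have about 97% power. But the size is given per group, and the analysis section does not mention pooling over margins. The point limits the concern to pairwise statements and does not remove it.

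**Conclusion.** The concern holds in a limited form. The size of 18 per group is consistent with about 80% power for an unadjusted or overall test, and it shows no allowance for the Bonferroni comparisons that follow. At 18 evaluable per group, an adjusted pairwise difference of 1.3 has about 53–63% power. Across the possible evaluable numbers, from a 30% loss to no loss, the range is 47–76%, below 80% throughout.

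A reader might go further and say that the trial misses its stated power, that its primary test is underpowered, or that a number is miscalculated. The article supports none of these: it prints no power, the primary test carries no adjustment, and 18 reproduces. The result rests on two-sided testing, on reading 1.3 and 1.4 as the between-group difference and SD of the 12-week change, and on three to six comparisons.

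**What to change.** **Statistical analysis.** Replace plain Bonferroni with a Shaffer step-down procedure. Run it only when the treatment-by-time test across the four arms is significant. The present wording lets any significant main effect open the post-hoc step, which could be time alone; that would not protect the error rate. State the family of comparisons:
- all six pairs: order the p-values and start at 0.05/3;
- three comparisons with control: start at 0.05/2.

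For six pairs at 18 per group, power rises from about 52–53% to about 57–62% (63% if two arms share the effect). This recovers only part of the loss.

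**Sample size and sampling.** When this paragraph is next revised, say that the size rests on an unadjusted or overall test, and give 53–63% as the power for adjusted pairwise comparisons. Name the sizing test only if the sponsor can confirm it from its own records.

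**Cost.** No extra patients, a few lines of code outside the default SPSS post-hoc menu, and no simple matching simultaneous confidence intervals. The stated power for pairwise claims will look less favourable.
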